### Outcomes

#### Primary outcomes

In addition to running performance (individual marathon finishing time of Step 3) adjusted to performance level the primary outcome is the prevalence of kinds of diets (omnivorous, vegetarian, vegan) among runners attending running events.

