### Trial objectives

The first and major goal of the NURMI Study is to compare endurance performance of vegetarian and vegan runners to non-vegetarian marathon runners and to determine potential differences/to identify possible correlations.The second goal is to investigate the prevalence of vegetarian and vegan runners in endurance (half-marathon and marathon) events.The third goal is to validate the subjects self-reports on his/her dietary behavior.

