**Fig. 1 Fig1:**
[figure not shown]
Timescale of the NURMI Study

### Step 1

Epidemiological pre-study

Step 1 is composed of a short standardized online questionnaire for endurance and ultra-endurance runners (any distance and any level of performance) primarily in Austria, Germany and Switzerland. Data on sex, age, kind of diet, and running history and habits will be collected. We aim to approach as many runners as possible for this step since gathered data will be used to estimate the prevalence of vegetarians and vegans active in endurance running.

### Step 2

The major NURMI Study questionnaire

Runners matching inclusion criteria of the respective subgroups (capable of running a half-marathon etc./see “Subjects” section) complete an extended questionnaire on health status, specific dietary habits (details of consumption of specific foods or food groups), running history (i.e. preferred running distance, finished races overall and number of completed races in the last 2 years, preparation for a specific event, average distance and training load per day/week, etc.) and exercise induced diet (i.e. during training, racing or a day of rest, nutritional strategy on race day, etc.) as well as quality of life and health-related behavior. Step 2 includes a short form of the Quality of Life questionnaire (QOL BREF 26) distributed by the World Health Organization.

### Step 3

NURMI post-race testing

After individual finishing a race of at least half-marathon distance, runners complete a questionnaire on final ranking, finishing time, energy and fluid intake, in race dietary strategy, and physical and mental perception. The rate of perceived exertion (RPE, overall, leg muscles and respiratory system) will be assessed by using the Borg Scale (Borg 1998).

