#### Inclusion criteria

For the epidemiological pre-study (Step 1) any subject active in running (any distance as well as any performance level) can participate. For successful participation in the main study (Step 2 and 3) a complete data set consisting of the following four items is required: written informed consent (1), at least 18 years of age (2), all NURMI questionnaires completed (3), successful participation in a running event of either half-marathon or marathon distance (4).

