#### Secondary outcomes

Outcomes from Step 1 are: nationality, sex, age, body weight, height, calculated BMI, kind of diet, attended races in past 2 years, finished running distances, personal best time on each distance, number of planned events for 2014/2015, in-race food and fluid consumption, daily/weekly training frequency, daily/weekly training load, period of preparation for main event, and aim of race participation.

Outcomes from Step 2 are: years of running experience, motivation for running then and now, assisted training, years of race experience, training intensity, medium/long-term goal of racing, additional specific kinds of training, specific diet including supplements, specific training/diet prior to race, diet on day of rest/training/race, pre/in/post-race diet, specific gear, relevant medical measures, and quality of life and health-related behavior.

Outcomes from Step 3 are: Pre-race: body weight (including clothing and shoes). In-race: individual finishing time, individual runtime as % of overall winners time (calculated), ranking, calculated pace, temperature, wind, air pressure, humidity, sunlight. Post-race: body weight (including clothing and shoes), calculated weight loss, RPE (Borg) whole body/respiratory/legs, mental mood, fluid and nutrient intake including breakfast, and dietary strategy during race.

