### Statistical methods

Analyses will be performed using commercially available software (IBM SPSS Statistics 23, SPSS Inc., Chicago, IL, USA). All data derived from the statistical methods will be given in mean ± standard deviation. Research shows that the most successful athletes in marathon and ultra-marathon running events are frequently those who lose substantially more than 3–4 % BW during competition (Zouhal et al. 2011). Mean body weight of male recreational marathon runners is 73.9 ± 8.1 kg (Barandun et al. 2012) and 75.8 ± 8.6 kg (Friedrich et al. 2014) of male recreational half marathon runners. Mean body weight of female recreational runners is 59.1 ± 6.3 kg (Rüst et al. 2013) and 60.1 ± 7.8 kg (Friedrich et al. 2014) of female recreational half marathon runners. Expected body weight loss during a marathon race is 2.3 ± 2.2 % overall (Zouhal et al. 2011). For male recreational marathon runners we expect a 2.3 % weight loss from 73.9 to 72.2 kg, therefore a sample size of 179 runners is needed to reach 80 % power with two-sided test and alpha of 0.05. For female recreational marathon runners we expect a 2.3 % weight loss from 59.1 to 57.7 kg, therefore a sample size of 159 runners is needed to reach 80 % power with two-sided test and alpha of 0.05. Since body weight loss during a marathon is inversely related to race finishing time (Zouhal et al. 2011) we expect the fastest runners to lose the most relative body weight during competition. Multi-variant regression analyses will be used the determine effects of kind of diet, sex, age, BMI, finished running distances, years of race experience, weekly training load, weekly training frequency, training intensity, in-race food and fluid consumption on individual finishing time (% of overall winners time, ranking, calculated pace). An analysis of variance will be performed to compare individual finishing time (% of overall winners time, ranking, calculated pace), sex, age, body weight, height, BMI, attended running events in past 2 years, finished running distances, personal best time on each distance, number of planned events for 2014/2015, daily/weekly training frequency, daily/weekly training load, period of preparation for main event, aim of race participation, years of running experience, motivation for running then and now, assisted training, years of race experience, training intensity, medium/long-term goal of racing, additional specific kinds of training, specific diet including supplements, specific training/diet prior to race, diet on day of rest/training/race, pre/in/post-race diet, in-race food and fluid consumption, specific gear, relevant medical measures, pre/post-race body weight (including clothing and shoes), calculated weight loss, in-race: nutritional strategy during race, fluid and nutrient intake including breakfast, mood status, and RPE (Borg) whole body/respiratory/legs, among the three subgroups created respective to diet.

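### The race behind the primary performance outcome is stated in three ways, and the planned diet comparison neither fixes one distance nor adjusts for it

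*Protocol article*

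**What the plan says.** All references are to the Protocol article.

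- Primary outcomes: performance is the "individual marathon finishing time of Step 3", adjusted in some unspecified way for performance level.
- Inclusion criteria, item 4, for Steps 2 and 3: "successful participation in a running event of either half-marathon or marathon distance".
- Methods, Step 3: the questionnaire is completed "After individual finishing a race of at least half-marathon distance". No upper limit is given.
- Trial objectives, first and major goal: to "compare endurance performance of vegetarian and vegan runners to non-vegetarian marathon runners". The second goal, on prevalence, names half-marathon and marathon events.
- Statistical methods, regression: the terms begin "effects of kind of diet, sex, age, BMI, finished running distances, years of race experience, weekly training load, weekly training frequency, training intensity" and end with in-race food and fluid intake. The response is finishing time expressed as a percentage of the winner's time, ranking and pace.
- Statistical methods, analysis of variance: the same responses, and many other variables, are compared across the three diet groups. Diet is the only factor named.
- Secondary outcomes: the covariate on finished distances is listed under Step 1, in the run "attended races in past 2 years, finished running distances, personal best time on each distance". The Step 3 list includes pace and weather but does not name race distance.

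**The concern.** The performance comparison between diets is the study's major goal, yet the article does not settle which finishers it covers. An analyst could use marathons only, half-marathons and marathons, or every Step 3 race, and could cite the article for each choice. That leaves room to choose after the data are seen.

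If more than one distance is analysed, a second problem follows. Pace falls as distance rises, ranking depends on the size and strength of the field, and the ratio to the winner's time need not be the same at two distances. Runners choose their own races. Under Subjects, they are recruited through separate channels, among them race websites, running magazines and magazines on vegetarian nutrition. Nothing in the design makes the distance mix equal across diets, and no listed model term would correct for an unequal mix.

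**Working it through.** **Step 1. Which finishers count under each section.**

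- Marathon finisher: has the primary performance outcome, meets item 4 of the Inclusion criteria, and is covered by Step 3.
- Half-marathon finisher: meets item 4 and is covered by Step 3, but has no value for an outcome defined as marathon time.
- Ultra-marathon finisher: is covered by the Step 3 wording, but that race does not meet item 4 and is not a marathon.

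Only the marathon finisher is treated alike in all three places.

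**Step 2. Does the analysis section settle it?** Statistical methods names no restriction to marathons and no distance stratum. Of the regression terms, only the one on finished distances could refer to the Step 3 race. Secondary outcomes places it in Step 1, between races attended in the past two years and personal best at each distance. Its natural reading is therefore race history. A runner who has completed both distances has the same history whichever one is run in Step 3.

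**Step 3. The plan's own figures.** The only sample sizes are 179 men and 159 women. They reproduce with a one-sample normal approximation, n = ((1.960 + 0.842) × SD / difference)²:

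- Men: SD 8.1 kg, difference 73.9 − 72.2 = 1.7 kg, n = 178.2, rounded up to 179.
- Women: SD 6.3 kg, difference 59.1 − 57.7 = 1.4 kg, n = 158.9, rounded up to 159.

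These figures concern body-weight loss in marathon runners. They do not bear on which races enter the diet comparison.

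**Step 4. Possible size on the pace scale.** The article gives neither the distance mix by diet nor pace by distance, so both inputs are assumptions. Let d be the difference between two diet groups in their half-marathon share, and r the proportion by which marathon pace is slower than half-marathon pace. With no diet effect at either distance,

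shift in mean pace, relative to half-marathon pace = d × r.

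With r from 4 % to 10 %:

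- d = 0: no shift.
- d = 0.10: 0.4 % to 1.0 %.
- d = 0.20: 0.8 % to 2.0 %.
- d = 0.30: 1.2 % to 3.0 %.

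On an assumed 240-minute marathon, the d = 0.20 range is about 0.008 × 240 = 1.9 min to 0.020 × 240 = 4.8 min.

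A second set of assumed values agrees. With means of 120 min for the half-marathon and 255 min for the marathon, pace is 120 / 21.0975 = 5.688 and 255 / 42.195 = 6.043 min/km. The gap is 0.355 min/km, or 21.3 s/km, which is 6.25 % of half-marathon pace. At d = 0.20 the shift is 4.3 s/km, or 1.25 %.

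**Step 5. Percentage of the winner's time.** If mean values at the two distances differ by an assumed 5 to 20 percentage points, d = 0.20 gives a shift of 0.20 × 5 = 1.0 to 0.20 × 20 = 4.0 points. If the distances do not differ on this scale, the shift is zero.

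**The case against.** The strongest reply is that a consistent reading exists. If Primary outcomes governs, the performance analysis is marathon only and there is no distance mix to adjust for. Half-marathon finishers remain eligible because they supply the secondary Step 3 outcomes, such as exertion, mood, intake and weight loss. Eligibility wider than the primary analysis set is not an error in itself. Step 3 merely says when the questionnaire is filled in, while the Inclusion criteria define a valid data set, so ultra-marathon races are already out. The mention of marathon runners in the first objective may be loose wording. The responses are scaled, and the article disclaims causal conclusions under Limitations of the study.

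Much of this stands. A reader might infer that distance is in fact confounded with diet here. The article does not support that: it gives no distance mix by diet, and a marathon-only analysis removes the issue. A reader might also compute a bias in raw minutes, for example 0.20 × (240 − 120) = 24 min. That does not fit the plan, because Further measurements and Statistical methods use percentage of the winner's time, ranking and pace, which take out the gross difference between distances. Nor can one conclude that ultra-marathon races will be analysed, since the Inclusion criteria can be read as excluding them.

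Two things remain. The marathon-only reading is nowhere stated in Statistical methods, so the reader has to supply it. And if half-marathons are kept, scaling does not guarantee comparability across distances. The phrase on adjustment to performance level does not fill the gap, because it names no variable and no method. The disclaimer on causality does not help either: a descriptive contrast between diets also misleads if it partly reflects which race was run.

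**Conclusion.** The point holds as an inconsistency in the definition of the primary performance outcome, together with a stated model that leaves Step 3 race distance uncontrolled if more than one distance is analysed. Confounding by distance is possible, not shown. It needs two conditions: the diet groups differ in distance mix, and distance still affects the scaled outcome.

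Under the assumed 4-10 % pace difference, a 20-point difference in mix moves mean pace by about 0.8-2.0 % without any diet effect. An equal mix moves it by nothing. Ranking depends on the event whatever the mix. The reading of the covariate on finished distances as race history is the natural one, but the wording in Statistical methods leaves some ambiguity.

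**What to change.** Reconcile Trial objectives, Methods (Step 3), Inclusion criteria, Primary outcomes and Statistical methods on which races count for the performance outcome, before the analysis begins. Then do one of the following:

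- If both half-marathon and marathon are kept, analyse performance within distance strata and combine the strata into one distance-stratified diet contrast, or add Step 3 race distance to the regression and to the analysis of variance. Interactions of distance with sex or age are not needed to cure this defect.
- If only the marathon is kept, state in Statistical methods that the primary performance analysis is restricted to marathon finishers.

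In either case, say whether the covariate on finished distances means race history or the race analysed. No new data are needed, because pace cannot be calculated without the race distance. The first option costs one extra stratification factor. The second costs the non-marathon entries in that analysis.

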#### Secondary outcomes

Outcomes from Step 1 are: nationality, sex, age, body weight, height, calculated BMI, kind of diet, attended races in past 2 years, finished running distances, personal best time on each distance, number of planned events for 2014/2015, in-race food and fluid consumption, daily/weekly training frequency, daily/weekly training load, period of preparation for main event, and aim of race participation.

Outcomes from Step 2 are: years of running experience, motivation for running then and now, assisted training, years of race experience, training intensity, medium/long-term goal of racing, additional specific kinds of training, specific diet including supplements, specific training/diet prior to race, diet on day of rest/training/race, pre/in/post-race diet, specific gear, relevant medical measures, and quality of life and health-related behavior.

Outcomes from Step 3 are: Pre-race: body weight (including clothing and shoes). In-race: individual finishing time, individual runtime as % of overall winners time (calculated), ranking, calculated pace, temperature, wind, air pressure, humidity, sunlight. Post-race: body weight (including clothing and shoes), calculated weight loss, RPE (Borg) whole body/respiratory/legs, mental mood, fluid and nutrient intake including breakfast, and dietary strategy during race.

### Strengths of the study

Since scientific data about endurance and ultra-endurance athletes following a vegan diet is limited the NURMI Study will be the first study to assess this issue considering a bigger sample size. The NURMI Study aims to provide a large data set comparing respective subgroups of omnivorous, vegetarian and vegan runners ranging from epidemiological aspects, dietary and training habits, in-race dietary consumption, and performance measurements. Large numbers of participants will allow to discriminate between and, identify associations with, different dietary patterns and level of training status as well as to detect differences in running performance between subgroups of omnivores, vegetarians and vegans. To make sure to assess fit runners only the NURMI Study focuses on runners who are at least capable of coping the half-marathon distance as the primary inclusion criteria.

### Limitations of the study

Not all vegetarians and vegans participating in running events may be within the reach of the various recruitment methods. Due to various season, daytime and location of races, environment conditions (e.g. weather including sun or rain, temperature, relative humidity) will vary among the respective running events. Furthermore, our study shares with others the limitation of the cross-sectional design; therefore the present investigation allows no conclusion regarding causality. Prospective cohort studies are needed to confirm the associations between specific kinds of diet, health status and endurance performance to assess the causal direction and to develop recommendations for nutritional intake for vegetarian and vegan runners for training and racing.

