#### Further measurements

Individual finishing time will be measured by the running events professional timing system and will be calculated as percentage of the overall winner’s time.

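### The finishing-time regression omits the race-day conditions that Step 3 records and has no event term, so pace is unadjusted for conditions and percent of the winner's time only partly adjusted

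*Protocol article*

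**What the plan says.** The Primary outcomes section names "running performance (individual marathon finishing time of Step 3) adjusted to performance level" beside the prevalence of diets, and Trial objectives puts the performance comparison first.

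For Step 3, the Secondary outcomes section lists among the in-race items "ranking, calculated pace, temperature, wind, air pressure, humidity, sunlight". Limitations of the study then acknowledges that "environment conditions (e.g. weather including sun or rain, temperature, relative humidity) will vary among the respective running events".

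Statistical methods gives an explicit covariate list. It begins with "kind of diet, sex, age, BMI, finished running distances, years of race experience, weekly training load, weekly training frequency" and ends with "training intensity, in-race food and fluid consumption on individual finishing time (% of overall winners time, ranking, calculated pace", the bracket holding the three expressions of the outcome. The list has no weather variable, no event term and no term for the distance of the Step 3 race. The analysis of variance across the three diet groups uses the same three expressions, again without these terms.

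One form of event-level scaling is planned. Under Further measurements, finishing time "will be calculated as percentage of the overall winner’s time".

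**The concern.** Participants choose their own race. Step 3 is open from March to December 2015, and the core region covers three countries, so races will differ in season and place. The article names the resulting variation in conditions as a limitation and plans to record the variables that describe it, but it does not use them in the model for its major goal.

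Two things are at stake. Variation between events that the model could explain stays in the residual and widens the intervals. And if one diet group tends to race in warmer or otherwise slower conditions, part of that difference is read as an effect of diet.

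Distance raises a related problem. Half-marathon and marathon are both eligible under Inclusion criteria. The covariate on finished distances is listed under Secondary outcomes as a Step 1 item of running history, so it does not identify the race that produced the outcome. Pooled pace would then mix two distances.

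**Working it through.** **The plan's own figures.** The only sample-size figures concern weight loss. With n = (SD × (1.960 + 0.842) / difference)², rounded up:

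- Men: (8.1 × 2.802 / 1.7)² ≈ 178.2, giving 179. This matches "a sample size of 179 runners is needed to reach 80 % power with two-sided test and alpha of 0.05".
- Women: (6.3 × 2.802 / 1.4)² ≈ 158.9, giving 159, also as stated.

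These figures say nothing about finishing time, so they neither support nor weaken the point.

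**What each expression of the outcome already handles.**

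- *Calculated pace*: no reference to the event, so it carries the full effect of conditions. At a fixed distance it is finishing time rescaled.
- *Percent of the winner's time*: a slowing common to winner and participant cancels in the ratio. Any slowing of the participant beyond the winner's remains, and so does variation in the winner's strength.
- *Ranking*: compares runners within one event, so weather shared by the field largely cancels. It depends on field size instead.

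**Illustration for pace (assumed inputs).** Suppose 60 % of one diet group and 40 % of another run in warm races that slow pace by 2-6 %. The spurious difference is (0.60 − 0.40) × 2 % = 0.4 % up to 0.20 × 6 % = 1.2 %. If conditions explain 5-15 % of outcome variance, adjustment multiplies standard errors by √(1 − 0.05) = 0.975 down to √(1 − 0.15) = 0.922, a narrowing of about 2.5-8 %.

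**Simulation (all inputs assumed).** 60 events of 10 runners, log finishing time with within-event SD 0.15, true diet effect zero, and a shared weather effect with SD 4 %. The log-odds that a runner belongs to the diet group are −0.5 + 0.5 per SD of weather. There were 600 replicates. Cells give the mean estimated diet effect, with its empirical SE in brackets.

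| Extra slowing of participants beyond winner (SD) | Winner strength (SD) | Raw time or pace | Percent of winner (log scale) | Within-event (event fixed effects) |
|---|---|---|---|---|
| 0 | 0 | 0.0182 (0.0138) | −0.0003 (0.0130) | −0.0002 (0.0140) |
| 0 | 8 % | 0.0177 (0.0135) | −0.0007 (0.0145) | −0.0006 (0.0133) |
| 3 % | 8 % | 0.0322 (0.0143) | 0.0134 (0.0150) | −0.0010 (0.0128) |
| 3 % | 15 % | 0.0325 (0.0146) | 0.0145 (0.0194) | −0.0007 (0.0132) |

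The bias follows the weather effect left in the metric:

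- Pace: 0.0182 / 0.04 = 0.46, and 0.0322 / 0.07 = 0.46 (4 % shared plus 3 % extra).
- Percent of winner: 0.0134 / 0.03 = 0.45.

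Under purely proportional slowing, percent of the winner's time shows no material bias. The within-event comparison shows none in any row. Its SE is lower than that of percent of winner by 1 − 0.0133/0.0145 = 8 % to 1 − 0.0132/0.0194 = 32 % in the last three rows. In the first row, where winner strength does not vary, it is 0.0140/0.0130 − 1 = 8 % higher.

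**The case against.** The strongest reply is that the plan already standardises to the event. Percent of the winner's time removes proportional slowing, and ranking is within event, so only pace lacks any event-level reference. The article also discloses the varying conditions and disclaims causal conclusions. All of this stands, and it limits the point.

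Several stronger readings are tempting but not supported:

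- *That all differences between events go unadjusted.* The scaling to the winner contradicts this.
- *That ranking is as exposed to weather as pace.* Its weakness is field size, not shared conditions.
- *That the diet comparison is confounded.* This needs diet to be associated with event conditions. Recruitment mixes organisers' websites and running communities with vegetarian and lifestyle magazines, which makes an association conceivable. The article says nothing about which races each group runs.
- *That runners from the same event are analysed as independent.* The article does not say how dependence within events is handled, and a condensed article may leave that to the full plan.

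The reply does not dispose of the omission itself. The covariate list is explicit, and it leaves out recorded variables that the article itself says vary between events. Disclosing a limitation does not replace adjusting for it when the data are available.

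**Conclusion.** The point holds in a limited form. Pace is unadjusted for event conditions. Percent of the winner's time is adjusted only for proportional slowing, at the price of noise from the winner's strength. Ranking is largely protected from shared weather.

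Some loss of precision is to be expected wherever conditions affect the metric. Bias is conditional on the diet groups racing in different conditions. The article gives no weather effect, no variance share and no distribution of events by diet, so the size cannot be derived. Under the assumed inputs, bias runs from about zero (percent of winner, proportional slowing) to about 1.3-1.5 % (percent of winner, 3 % extra slowing of participants), and is about 1.8-3.3 % for pace. These figures show the mechanism and are not estimates for this study.

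The distance term matters only if half-marathon and marathon results are pooled. The primary outcome refers to marathon time, but eligibility covers both distances.

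This is a worthwhile, inexpensive improvement to the model for the study's major goal. It is not a flaw that invalidates the plan.

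**What to change.** In Statistical methods, add three covariates, at least to the models for pace and percent of the winner's time: recorded temperature, recorded humidity, and the distance of the Step 3 race actually run (half-marathon or marathon).

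Where enough participants share an event, add a sensitivity analysis with event fixed effects, defining an event by race, date and distance. Diet groups are then compared within the same event, and weather terms shared by all its runners drop out. A random event effect alone is not a substitute: it still uses differences between events and does not generally remove confounding when diet share varies with conditions.

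The cost is one or two sentences and a few degrees of freedom. Some weather entries will be missing and may have to be filled from the date and place of the race. The fixed-effects analysis draws only on events that include more than one diet group, which is why it is proposed as a sensitivity analysis.
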